#### Usual Care Onboarding Meeting With Research Coordinator

After completion of informed consent and the baseline measures, the research coordinator meets with the participant by Zoom to review the study procedures. Like participants in the ExerciseRx app group, the coordinator reviews the recommended physical activity guidelines for adults with MS and provides print resources for increasing physical activity, identical to what materials the ExerciseRx participants receive.

#### 26-Week Usual Care Period

Usual care participants are instructed to carry their phone throughout the day to allow passive collection of step counts during the study period; however, they will not be able to view or use any of the features of the ExerciseRx app. Participants are not discouraged from engaging in physical activity, and providers are not precluded from providing whatever care they usually would to their patients during the study period.

#### Post Follow-Up Phase

After the final (26-weeks) outcomes are collected, usual care participants are offered the ExerciseRx platform, which is delivered as described above.

### Assessment Procedures and Measures

#### Overview

All participants complete baseline and outcome assessments using REDCap, a web-based data capture platform [28] that can be completed by any digital device with internet access. It includes a human verification service (reCAPTCHA) to avoid responses from bots. Outcome assessments are collected at baseline, post a 12-week treatment period (primary end point), and at a 3-month follow-up after the treatment period. We obtain step count data from all participants throughout the trial and collect data from all randomized participants, regardless of their adherence to treatment (ie, intent-to-treat). Participants receive up to US $150 remuneration for completing the REDCap assessments (US $50 for each assessment point).

#### Participant Characteristics

Participants provide demographic variables, including self-reported sex assigned at birth, gender identity, age, race, ethnicity, employment status, relationship status, and education level. Clinical information, including MS subtype, time since diagnosis, and medications (including disease-modifying therapy), is obtained from chart review. MS disease severity (assessed using the PDDS, a brief self-reported assessment that has been found to be a valid measure of disease severity in an MS population [31]), occurrence of clinical relapses (over the preceding 6 months and throughout the study period), and self-reported falls (over the preceding 6 months and throughout the study period) are also assessed. Data on other treatments and therapies used during the study period (active treatment and follow-up) are collected via medical record extraction and self-report.

#### Primary Outcome: Step Count

For the week before (baseline) and throughout the 12-week intervention period, step count will be measured within the ExerciseRx app, which passively collects step count data from device sensors using Core Motion, Google Fit, and Google Health Connect. Participants in the usual care condition will also have their step count passively monitored via the ExerciseRx app on their smartphones. Step count is an ideal primary outcome in physical activity promotion trials because it provides an objective, quantifiable measure of daily activity that is sensitive to change and free from self-report bias. It captures both structured and incidental movement, is easy to interpret for participants and clinicians, and is associated with meaningful improvements in health and function [35], including in adults with MS [36,37]. It is possible that step count may be underestimated due to a lack of carrying time or location; a few studies have shown that carrying a phone in a pocket or purse can lead to underestimations of step count [38,39]. However, since this study is looking primarily at changes and trends in step count over time, with consistent phone carrying behaviors, clinically relevant assessments will still be obtained [38,40].

#### Secondary Outcomes: Physical Activity

The International Physical Activity Questionnaire-Short Form, which is validated for MS [41,42], will be given to participants at baseline to assess frequency and intensity of physical activity at each assessment timepoint. Activity intensity and frequency will then be used to calculate total MET-minutes per week for participants in each condition. The Physical Activity Vital Sign (described above) will also be obtained at each timepoint to determine the percentage of participants in each group that progress their total minutes spent in moderate to vigorous intensity physical activity per week toward the current physical activity guidelines (of >150 min of moderate intensity or >75 min of vigorous activity per week).

#### Secondary Outcomes: Symptoms and Function

The following patient measures, all validated in MS, are obtained at the three outcome timepoints to investigate the effects of the ExerciseRx platform on symptom severity: Patient-Reported Outcomes Measurement Information System (PROMIS) pain intensity (PROMIS Pain Intensity Short Form) [43,44], fatigue severity (PROMIS Fatigue Intensity Short-Form)[43,45], depressive symptom severity (PROMIS Depression Short-Form) [43,46], and sleep disturbance (PROMIS Sleep Disturbance Short Form) [43,47]. We will also assess functional outcomes, specifically physical functioning (PROMIS Physical Function 10a) [48], pain interference (PROMIS Pain Interference Short-Form) [43,44], fatigue interference (PROMIS Fatigue Impact Short Form) [43,45], social participation (PROMIS Satisfaction with Participation in Social Roles Short Form 8a) [43], and self-reported falls (during the 6 months prior to randomization and throughout the study period).

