**Figure 2 figure2:**
[figure not shown]
The ExerciseRx app example screenshots.

This paper describes the rationale, aims, and protocol for the ExerciseRx-MS Trial, a randomized controlled trial designed to answer whether the ExerciseRx platform improves physical activity and other common symptoms and functional outcomes in adults with MS who are insufficiently active. The first aim is to evaluate the efficacy of the ExerciseRx platform relative to usual care in increasing physical activity, measured by average daily step count (primary outcome), activity volume, and the proportion who meet exercise guidelines in adults with MS who are insufficiently active. We hypothesize that participants randomized to the ExerciseRx app group will show a greater increase in physical activity at 12 weeks, as measured by daily average step count (primary outcome) and by total metabolic equivalent minutes of activity per week (secondary outcome) relative to participants randomized to usual care. We also hypothesize that a higher proportion of participants in the ExerciseRx app group will increase their minutes per week of moderate to vigorous intensity aerobic activity at 12 weeks (secondary outcome), relative to usual care participants.

The second aim is to evaluate the efficacy of the ExerciseRx platform relative to usual care on secondary outcomes, specifically symptoms (fatigue intensity, pain intensity, sleep, and depressive symptoms) and patient-reported functional outcomes (physical functioning, fatigue interference, pain interference, falls, and social participation). We hypothesize that participants in the ExerciseRx platform group will show greater improvements in secondary outcomes at 12 weeks relative to usual care participants. Additional secondary analyses will test maintenance of any treatment effects at a 3-month follow-up. We will also explore moderators of immediate (post-12 weeks) and 3-month follow-up outcomes, including demographics, disease course, and baseline participant factors (including fatigue, pain, depression, activity level, BMI, exercise self-efficacy, and disability) to explore potential moderators of treatment effects that can be evaluated a priori in future effectiveness and mechanistic research.

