### Recruitment, Enrollment Procedures, and Eligibility Criteria

The primary recruitment sources are referrals from clinic providers (physiatrists, neurologists, nurse practitioners, nurses, and psychologists) and the research registry. The EHRs of patients who are potentially interested in and eligible for the study are prescreened by a research coordinator to confirm MS diagnosis [26,27]. The coordinator then meets with the potential participant by phone to complete a standardized eligibility safety screening to ascertain eligibility. Staff track the recruitment outcomes for everyone who is screened, including reasons for ineligibility or declination. Basic demographic and MS disease characteristics (MS duration, course, and date of diagnosis) are obtained for those considered eligible who decline to enroll; this deidentified information will be used to compare them to study participants to assess the sample’s generalizability. All consent procedures are via REDCap (Research Electronic Data Capture; Vanderbilt University), an open-source, secure, HIPAA-compliant web-based platform for data capture (including e-consent and outcome survey administration) [28].

Inclusion criteria are (1) provider-confirmed diagnosis of MS; (2) 18 years of age or older; (3) Patient Determined Disease Steps (PDDS) score <3, indicating the potential for some gait disability although typically ambulates without an assistive device; [29-31] (4) insufficiently active, defined as <150 minutes of moderate intensity physical activity per week per the US National Physical Activity Guidelines, assessed using the Physical Activity Vital Sign [26,27,32] during screening; and (5) use of an iPhone with software version iOS14+ or an Android phone with version 5+. Exclusion criteria are (1) recent (past 4 weeks) or planned surgery during the study period which may impact step counts; (2) MS relapse within the last 30 days; (3) plans during the study period which may impact a participant’s daily access to Wi-Fi, which could interfere with server uploads of mobile phone data; (4) >3 falls in the past 6 months; and (5) contraindication to exercise.

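### Falls over the 6 months before randomisation should be a covariate, not a repeated outcome value alongside falls counted over about 12 to 13 weeks

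*Protocol article*

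**What the plan says.** The Introduction lists falls among the Aim 2 outcomes: "patient-reported functional outcomes (physical functioning, fatigue interference, pain interference, falls, and social participation". The hypothesis for that aim is comparative and dated: "We hypothesize that participants in the ExerciseRx platform group will show greater improvements in secondary outcomes at 12 weeks relative to usual care participants".

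The observation period appears twice. Secondary Outcomes: Symptoms and Function gives "self-reported falls (during the 6 months prior to randomization and throughout the study period", and Participant Characteristics gives "self-reported falls (over the preceding 6 months and throughout the study period) are also assessed". Neither section states the period a participant is asked about at each later assessment.

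The timing comes from the Overview of Assessment Procedures and Measures: "Outcome assessments are collected at baseline, post a 12-week treatment period (primary end point), and at a 3-month follow-up after the treatment period". The Post Follow-Up Phase section puts the last assessment at 26 weeks: "After the final (26-weeks) outcomes are collected, usual care participants are offered the ExerciseRx platform". Eligibility excludes people with ">3 falls in the past 6 months".

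Sample Size, Power, and Analysis Plan specifies for step count a linear mixed model with week, treatment, their interaction and a random intercept. It then extends similar models to every secondary outcome, with the measure itself as the dependent variable. It mentions no rate, offset or follow-up time. Secondary findings are labelled hypothesis-generating.

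**The concern.** The PROMIS scales and activity questionnaires can serve as repeated measures, because a score at baseline and a score at 12 weeks are on one scale. A fall count is on one scale only if the windows are equally long. Here the baseline window is 6 months, while the period from randomisation to the hypothesised endpoint is about 12 weeks. Taken literally, the model uses a count over about 26 weeks as the baseline value of an outcome whose later values probably cover 12 to 13 weeks.

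Two things are at stake. A table of raw mean falls by visit would show a large drop in each arm with no change in risk, and in a trial that asks people to walk more, that could be taken as reassurance. The between-arm estimate would also carry the noise of a longer, more variable baseline count that need not be part of the outcome.

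**Working it through.** **The plan's own figure.** No figure is given for falls. The stated power is for step count: 45 per arm, d = 0.60 and two-sided 0.05 give 80.4% (noncentral t, 88 df), and 90/0.85 rounds up to 106. Both agree with the article. The 45 per arm is used below.

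**Inputs from the article.** Baseline window 6 months, about 26 weeks; first post-randomisation interval about 12 weeks; second about 13 weeks; baseline count capped at 3 by eligibility.

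**Assumptions.** Later counts cover the time since the previous assessment. Falls follow a gamma-Poisson distribution with a mean of 0.7 to 1.2 per 6 months before the cap. The article gives no fall rate. Week is treated as categorical, so with complete data the week-12 interaction equals the between-arm difference in change from baseline.

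**1. Within-arm change with no effect.** Expected count = rate × window.
- 12 weeks: 12/26 = 0.46 of baseline, an apparent drop of 54%.
- 13 weeks: 13/26 = 0.50 of baseline, an apparent drop of 50%.

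The cap at 3 pulls the other way, because people selected for a low baseline count drift upward. In a simulation with a mean of 1 fall per 6 months before the cap, the control arm changed by −0.33 falls on raw counts and +0.14 on counts rescaled to 6 months. The two figures imply a follow-up mean f with f × (26/12 − 1) = 0.47, so f = 0.40 and baseline is about 0.74. The follow-up count is then 0.55 of baseline, still close to a halving. A paired test in the control arm was significant in 60% of runs on raw counts and 7% on rescaled counts.

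**2. Between-arm contrast with no effect.** With k = 12/26 and baseline rates a and c, the contrast is (k − 1)(a − c), which is 0 when a = c. The same simulation (45 per arm, 4,000 runs) gave a mean difference of 0.001 and 4.5% rejection.

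**3. Chance imbalance.**
- a = 1.2, c = 1.0: −0.538 × 0.2 = −0.11 falls.
- a = 1.5, c = 1.0: −0.538 × 0.5 = −0.27 falls.

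Both favour the arm with more baseline falls. For comparison, a true 30% reduction at 1 fall per 6 months is 0.30 × 12/26 = 0.14 falls. In simulation, the arms' observed baseline means differed by at least 0.2 falls in about 27% to 33% of trials. Each 0.2 moved the change contrast by about 0.15 to 0.17 falls.

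**4. Variance.** With no heterogeneity between people and no cap, the change score has variance r + rk and the follow-up count rk. The ratio is (1 + k)/k, which is 3.0 for k = 13/26 and 3.2 for k = 12/26. Heterogeneity lowers it, since baseline then predicts follow-up. With the cap, and gamma shapes from 0.5 to 2, the variance of the change contrast divided by that of the baseline-adjusted post-randomisation contrast ran from about 1.7 to 2.6. It rises towards 3.0 as counts approach Poisson. The working range is therefore about 1.7 to 3.0.

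**The case against.** The strongest reply is that the planned test is a comparison between arms. The difference in window length is the same in both randomised arms and is absorbed by the week effect. That is correct. A reader might infer from the unequal windows that the treatment benefit itself will be misstated; step 2 shows no bias in expectation and no inflation of type I error. Nor does it follow that a true 30% reduction would be reported as about 14% or 15%. That figure appears only if a 12- or 13-week difference is divided by a 26-week baseline, and the article nowhere says effects will be expressed so. Against the concurrent control arm the full 30% is seen.

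Second, the later recall window is inferred from visit spacing. Over the whole study, falls before and after randomisation cover similar lengths of about 6 months, so a final comparison could be matched. That stands, but it does not serve the 12-week hypothesis. If 6-month recall were instead repeated at the first follow-up, more than half of that window would precede randomisation. The article does not say that this is done.

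Third, rates and offsets are often left to a full analysis plan, and the paired tests are described for the primary aim and not expressly for falls. This limits the point to what the article does state: the baseline window, the timing of the hypothesis and the form of the model. Those three do not fit together for falls.

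Fourth, falls related to study participation are tracked separately as adverse events, and a drop common to both arms would not hide an excess in one of them when arms are compared. That also stands. The worry about false reassurance applies to within-arm figures only.

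**Conclusion.** The point holds as one of interpretability and precision, and not as one of bias. If later counts cover the time since the previous assessment, raw within-arm change would show a spurious drop of about half. The planned interaction remains valid under randomisation, but treating the 6-month count as a baseline outcome value costs about 1.7 to 3.0 times the variance of the adjusted alternative. It also leaves the single trial's estimate open to baseline imbalance of a size comparable with a plausible effect. These magnitudes rest on assumed rates of 0.7 to 1.2 falls per 6 months, gamma-Poisson counts and 45 per arm. The qualitative result needs only unequal windows. The matter concerns one hypothesis-generating secondary outcome, so it is a worthwhile and nearly free improvement and no threat to the trial's main conclusion.

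**What to change.** - State the recall window used for falls at each assessment.
- Define the outcome as post-randomisation falls per person-time, from randomisation to week 13 and from randomisation to week 26, using each participant's actual follow-up. A count model with log follow-up time as offset does this and also handles participants who leave early.
- Compare the arms with the 6-month pre-randomisation count as a covariate and not as a repeated outcome value.
- Report falls by arm as rates, and give no raw change from baseline.

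The cost is mainly analysis wording, and the article dates the start of analysis to January 2026. Recall wording needs attention only if a 6-month question is being repeated at follow-up. The drawbacks are that no change-from-baseline figure for falls will be available and that falls need a model separate from the other secondary outcomes. The primary outcome and the sample size do not change.

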#### Exploratory Mechanisms: Moderators

We will use baseline values of the demographic, clinical, and symptom measures, exercise self-efficacy [49], and BMI to explore moderators of immediate (post 12 weeks) outcomes that may be evaluated a priori in future effectiveness and mechanism research on the ExerciseRx platform.

#### Implementation Measures

Both quantitative and qualitative implementation measures will be completed by participants in the ExerciseRx app group after they have completed the 12-week treatment period. Quantitative measures will include ratings of ease of use, interface, satisfaction, and usefulness from the mHealth App Usability Questionnaire [50]. Participants’ app engagement will be measured via the ExerciseRx platform data, which tracks the frequency of logins and completion of weekly barriers or facilitators in-app surveys. Providers will also complete a similar brief survey of implementation factors, including measures of acceptability, satisfaction, demand or engagement, usability, and integration of the ExerciseRx platform into their clinic workflows. The ExerciseRx platform will provide data on providers’ frequency of and engagement with the provider dashboard of the ExerciseRx platform, including logins, screen interactions, and messages sent to participants.

In addition to the participant and provider self-report usability measures, we will conduct semistructured interviews with 14 individuals who receive the ExerciseRx intervention and at least 3 providers to better understand their experiences on study completion, including usability and feasibility of the platform. The semistructured interviews are informed by (1) the Lived Informatics Model [51], which describes key stages of using health tracking apps: deciding to track, selecting a tool and tracking plan, collecting data, integrating it, reflecting on it, lapsing, and resuming use; and (2) goal directed self-tracking, which supports examining how the functionality and design of a tracking app aligns with their activity goals [52]. The interview guide is provided in Multimedia Appendix 1. Interviews will include information regarding demographics, open-ended questions about barriers or facilitators to physical activity and use of technology, and app features feedback. Interviews will be conducted over Zoom, recorded, transcribed, and double-coded with two coders using Dedoose software (SocioCultural Research Consultants, LLC).

#### Safety

We are tracking any adverse events, including falls or injuries related to study participation per University of Washington Human Subjects Division procedures, which include monitoring for possible adverse events, managing them, and reporting them to the principal investigator, Human Subjects Division, and study sponsor, as indicated. Since the ExerciseRx app is a wellness platform that helps patients to meet current national physical activity guidelines, the regulatory pathway is Software as a Medical Device Class I (low risk, exempt).

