#### Provider Dashboard and Interactions

A total of 7 MS providers (2 physiatrists, 4 neurologists, and 1 psychologist) are the providers in this study. Each provider can view on the provider dashboard of the ExerciseRx platform: (1) a triaged aggregate patient panel that depicts their patients’ progress in meeting weekly goals; (2) clinical decision support recommendations for next steps (eg, reactions and message suggestions); and (3) individual participant weekly step count and most common barriers or facilitators (obtained from the surveys completed weekly by participants). The providers check and act on the dashboard at least once a week during the study period. They can offer feedback and reinforcement via the provider dashboard of the ExerciseRx platform, which sends the patient messages via app notifications. For example, if a patient is at less than 75% of their goal by the 3rd week, their MS provider can send them a nudge from the provider dashboard.

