#### Low Engagement Support Protocol

The app monitors participants’ engagement and sends automated notifications to the provider and research coordinator. For example, if a patient has not opened the app in 5 days, they receive the following support message: Tech support message #1: “Hello, we noticed you haven’t opened the ExerciseRx app recently. Are you having any difficulties with the app or accessing Wi-Fi or cellular connection? Please let us know if there is anything we can assist you with.” The research coordinator monitors the responses and patient inquiries and provides responses or technical assistance if needed. They also connect the patient to the provider to answer questions as needed; providers can also reach out to participants if they wish.

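### Falls are counted over 6 months at baseline but about 12 to 13 weeks at the primary end point, with no common time scale stated, so an unchanged fall rate would look like a drop of about half

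*Protocol article*

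**What the plan says.** The Introduction, under the second aim, lists falls among the "patient-reported functional outcomes (physical functioning, fatigue interference, pain interference, falls, and social participation" and hypothesizes greater improvement at 12 weeks with ExerciseRx than with usual care.

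The section Secondary Outcomes: Symptoms and Function defines the measure as "self-reported falls (during the 6 months prior to randomization and throughout the study period". Participant Characteristics agrees: "self-reported falls (over the preceding 6 months and throughout the study period) are also assessed". Neither place makes relatedness to the study a condition.

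Collection is the same in both arms: "All participants complete baseline and outcome assessments using REDCap", and "Outcome assessments are collected at baseline, post a 12-week treatment period (primary end point), and at a 3-month follow-up after the treatment period". Study Limitations places the follow-up assessments at 13 and 26 weeks.

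Sample Size, Power, and Analysis Plan specifies, for steps, a linear mixed model with week, treatment, their interaction and a random intercept. It names paired and independent t tests as post hoc analyses. Similar models are to be used for each secondary outcome. No scaling of falls by observation time is mentioned.

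The Safety section covers falls a second time, in different terms: "We are tracking any adverse events, including falls or injuries related to study participation per University of Washington Human Subjects Division procedures".

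**The concern.** A fall count is meaningful only together with the time over which it was collected. The baseline looks back 6 months. At the primary end point the study period has lasted only 12 to 13 weeks, so a follow-up count has had about half as long to accumulate. If both counts enter one linear model as they stand, the time effect mixes any real change with the change in window length.

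This matters because the intervention asks people with MS to walk more, which makes falls a natural harm question as well as an efficacy outcome. A report that falls halved in the app arm would be reassuring and could be entirely an artefact. A real rise in the fall rate could be hidden in the same way.

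The relatedness qualifier in the Safety section raises a second, smaller issue. Falls would be described on two bases: one attached to study participation, the other unconditional. A reader of the results would need to know which one a table of falls uses.

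**Working it through.** The documents give no fall rate and no figure for falls, so there is no stated result to reproduce. The sample size calculation concerns step count, and this point does not depend on it.

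**Inputs**
- Baseline window: 6 months, taken as 26 weeks (Secondary Outcomes: Symptoms and Function).
- Follow-up window at the primary end point: 12 weeks (Assessment Procedures and Measures, Overview) to 13 weeks (Study Limitations).
- Entry limit: people with more than 3 falls in the past 6 months are excluded (eligibility criteria).

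**Step 1: apparent change at a constant rate.** With weekly rate r, the expected baseline count is 26r and the expected follow-up count is 12r or 13r.
- 12 weeks: 12/26 = 0.46, an apparent drop of 54%.
- 13 weeks: 13/26 = 0.50, an apparent drop of 50%.

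A participant at the entry limit, with 3 falls in 6 months and no change in rate, would be expected to report 3 × 12/26 = 1.4 to 3 × 13/26 = 1.5 falls.

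**Step 2: between-arm contrast under the null.** If both arms have the same rate r throughout, each arm's expected raw change is 12r − 26r = −14r. The difference between arms is −14r − (−14r) = 0. The interaction is centred at zero.

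**Step 3: noise in the change contrast.** Assume that each participant's falls follow a Poisson process with a personal rate that is constant over time, with mean λ and variance τ² across participants. Assume also complete data and time as a category, so that the interaction is the difference in mean change. The entry limit is ignored. These are illustrative assumptions, not figures from the documents.
- Raw change (follow-up minus baseline), 12 weeks: variance = 12λ + 26λ + (12 − 26)²τ² = 38λ + 196τ².
- Baseline first rescaled to 12 weeks: variance = 12λ + (12/26)² × 26λ = 12λ + 5.54λ = 17.54λ. The τ² term cancels.
- Ratio with τ² = 0: 38/17.54 = 2.17. With 13 weeks: 39λ/(13λ + 6.5λ) = 2.0.

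Both contrasts estimate the same between-arm difference in follow-up falls, but the raw one has at least 2.0 to 2.2 times the variance, and more if participants differ in their underlying rate. One consequence is that a chance baseline imbalance of δ falls per week produces a raw difference in change of −14δ at 12 weeks, even when no one's rate changes.

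**Step 4: the two descriptions of falls.** In Safety, the relatedness phrase follows falls or injuries, within a sentence that begins with any adverse events. In Participant Characteristics and in Secondary Outcomes, falls are self-reported without that phrase. The article does not say which basis a summary of falls would use.

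**The case against.** The strongest reply is that the trial tests a difference between arms, and Step 2 shows that equal windows leave that test centred correctly under the null. This stands, and a reader who infers that the window mismatch biases the treatment effect goes too far. It does not rescue statements about within-arm change, and it does not remove the extra variance.

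A second reply is that the article states neither the recall window of the follow-up question nor the scaling of falls, that both are commonly left to a full protocol or SAP, and that 26 weeks of study period roughly match the 6-month baseline. This stands in part. At the final assessment a cumulative count would indeed be comparable. At the primary end point it cannot be, and the article does fix the baseline window, the 12-week hypothesis and the type of model.

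A reader might also infer that the comparison of harms is uneven by construction. Only app participants have a weekly survey, and for them "The providers check and act on the dashboard at least once a week during the study period" and "The research coordinator monitors the responses and patient inquiries and provides responses or technical assistance if needed". The relatedness qualifier could also seem to admit falls in the app arm only. The documents do not support that reading:
- The Safety sentence covers any adverse event and sets no difference by arm.
- Controls also meet the coordinator and receive the same activity guidance and print materials, so a control's fall could be related to participation.
- The weekly survey concerns barriers and facilitators, and the example in the low-engagement protocol is a technical-support message. Neither is described as an adverse event query.
- No between-arm comparison of adverse events is planned.
- Falls as an outcome are self-reported by both arms on one schedule.

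The method of adverse event collection, including any common item on non-fall injuries, may lie in the full protocol or institutional procedures, which are not shown. Its absence from the article is not a finding.

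**Conclusion.** The point holds for the falls outcome at the primary end point. If raw counts are modelled as the article describes, a constant fall rate appears as a 50% to 54% reduction in each arm. This rests on taking 6 months as 26 weeks and on the week-12 or week-13 report covering only the time since the study period began. The between-arm interaction is not biased under the null. Its variance is about twice what a common time scale would give, or more, under the Poisson assumptions above.

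The relatedness wording in Safety is a matter for clarification only. The documents give no basis for claiming unequal ascertainment of falls between arms, or for putting a size on such a difference for other events.

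**What to change.** In Secondary Outcomes: Symptoms and Function, state the window that each falls report covers, including whether the 26-week report is cumulative or runs from the previous assessment. In the analysis plan, take falls out of the common linear model and analyse them as a rate per person-time in both arms. One suitable form is a Poisson or negative binomial model with log exposure time as an offset, reported as a rate ratio. Use the REDCap self-reports, whether or not a fall is thought related to the study.

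In Safety, reconcile the relatedness phrase with the unconditional collection of falls. State that any between-arm summary of falls uses the common REDCap reports, and that events coming to light through the app, the dashboard or the coordinator are listed separately.

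The cost is small. No new data are needed, provided that the period covered by each report is known, and the change can be fixed before the analysis planned from January 2026. Falls would be reported on a different scale from the other secondary outcomes, and the model must allow for overdispersion. Scaling does not make within-arm change a clean estimate, because eligibility limits falls before entry. Inference should rest on the between-arm rate ratio.
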